# Transitions Between Circulatory States After Out-of-Hospital Cardiac Arrest: Protocol for an Observational, Prospective Cohort Study

**DOI:** 10.2196/resprot.8558

**Published:** 2018-01-19

**Keywords:** out-of-hospital cardiac arrest, critical care, hemodynamics, inflammation, biomarkers

## Abstract

**Background:**

The post cardiac arrest syndrome (PCAS) is responsible for the majority of in-hospital deaths following cardiac arrest (CA). The major elements of PCAS are anoxic brain injury and circulatory failure.

**Objective:**

This study aimed to investigate the clinical characteristics of circulatory failure and inflammatory responses after out-of-hospital cardiac arrest (OHCA) and to identify patterns of circulatory and inflammatory responses, which may predict circulatory deterioration in PCAS.

**Methods:**

This study is a single-center cohort study of 50 patients who receive intensive care after OHCA. The patients are followed for 5 days where detailed information from circulatory variables, including measurements by pulmonary artery catheters (PACs), is obtained in high resolution. Blood samples for inflammatory and endothelial biomarkers are taken at inclusion and thereafter daily. Every 10 min, the patients will be assessed and categorized in one of three circulatory categories. These categories are based on mean arterial pressure; heart rate; serum lactate concentrations; superior vena cava oxygen saturation; and need for fluid, vasoactive medications, and other interventions. We will analyze predictors of circulatory failure and their relation to inflammatory biomarkers.

**Results:**

Patient inclusion started in January 2016.

**Conclusions:**

This study will obtain advanced hemodynamic data with high resolution during the acute phase of PCAS and will analyze the details in circulatory state transitions related to circulatory failure. We aim to identify early predictors of circulatory deterioration and favorable outcome after CA.

**Trial Registration:**

ClinicalTrials.gov: NCT02648061; https://clinicaltrials.gov/ct2/show/NCT02648061 (Archived by WebCite at http://www.webcitation.org/6wVASuOla)

## Introduction

### Post Cardiac Arrest Syndrome

Recent advances in cardiopulmonary resuscitation (CPR) have improved the chance of successful return of spontaneous circulation (ROSC) after cardiac arrest (CA) [1,2]. This implies that patients, who previously died during CPR, now obtain ROSC and are admitted to hospitals for further treatment. However, in-hospital mortality is unchanged at around 50% to 70% [3-5]. The post cardiac arrest syndrome (PCAS) is responsible for the majority of in-hospital deaths after CA. PCAS includes (1) brain injury, (2) myocardial dysfunction, and (3) systemic ischemia and reperfusion injury. In addition, the pathological process that caused the CA and other chronic diseases influences the clinical course of PCAS. Circulatory support after CA usually follows recommendations similar to those used for treatment of septic shock [6-9]. Septic shock and PCAS share some characteristics and experiences from the treatment of septic shock, such as emphasis on oxygen deliverance, which may be useful [10,11]. However, PCAS is a different clinical entity than septic shock, and circulatory failure after CA may have special characteristics [4]. This is exemplified by the need to perfuse the postischemic brain without unnecessary strain on the postischemic heart.

### Inflammation and Circulatory Failure

Circulatory failure after CA is both due to cardiac etiologies and systemic inflammatory response elicited by the hypoxic insult and reperfusion, but the relative contribution of each factor is unknown. The balance between pro- and anti-inflammatory cytokine signals is important in the development of organ failure [12]. Several studies have explored cytokine plasma concentrations as biomarkers for severity, risk of organ failure, and mortality in sepsis [13-15]. By comparison, only 4 studies in humans, with data from 2 patient populations, have evaluated the inflammatory response in PCAS [10,16-18], and 2 studies have explored the endothelial activation and injury in relation to inflammation in PCAS [18,19]. Furthermore, none of these studies specifically investigated the relationship between endothelial injury, inflammatory response, and circulatory failure.

In a cohort study from 2002, 73 out of 165 normothermic patients treated for out-of-hospital cardiac arrest (OHCA) developed circulatory instability, with median onset 6.8 hours after OHCA. [20]. Low cardiac output (CO) and filling pressures characterized the circulatory instability. The CO improved after 24 hours but superimposed vasodilatation developed, requiring fluid administration and use of vasoactive medications. Most patients recovered within 3 days, and hemodynamic status did not predict neurologic outcome [20]. In a Norwegian study, these results were confirmed in hypothermic CA patients [21]. In contrast, in the *Target Temperature Management Trial*, which randomized CA patients to either 33°C or 36°C, the circulation of patients in both groups were characterized by vasoconstriction [5,22,23]. However, the variables in studies on circulatory failure after CA are highly dependent on the use of vasoactive medications, and some studies are difficult to interpret because of limited information about the use of these medications.

### Rationale for a New Study

The International Liaison Committee on Resuscitation consensus statement from 2008 acknowledges the lack of knowledge about optimal treatment of PCAS and how to best deliver circulatory support after CA [4].

This protocol describes a study aimed to investigate patients with ROSC after OHCA, regarding (1) characteristics of circulatory failure in PCAS; (2) the endothelial and inflammatory response in PCAS; and (3) the relationship between circulatory failure and the inflammatory and endothelial response in PCAS.

## Methods

### Research Questions

This study will address the following research questions:

What are the characteristics of circulatory failure in PCAS?What are the characteristics of transitions between different clinical circulatory states during PCAS?What is the inflammatory response measured by inflammatory and endothelial biomarkers in PCAS?Which clinical characteristics and biomarkers predict changes in clinical circulatory states?

### Study Design

This study is a single-center, prospective, observational cohort study.

### Setting

The study will take place at the intensive care unit (ICU) and the coronary care unit (CCU) at the St. Olav’s University Hospital, a tertiary referral university hospital in Trondheim, Norway, with a catchment population of 700,000.

### Eligibility

#### Inclusion

All adult patients who are admitted to either the ICU or the CCU with obtained ROSC after OHCA will be considered for inclusion. Inclusion is performed immediately after arrival to the ICU or CCU.

#### Exclusion Criteria

Exclusion criteria are age <18 years, CA of septic or anaphylactic origin, sepsis within 24 hours before CA, pregnant women, transferred from other hospitals after OHCA, and decision to not initiate life-sustaining therapy after hospital arrival.

### Censoring

Patients are censored from further follow-up if the patient undergoes acute cardiothoracic surgery or intervention with extracorporeal membranous oxygenation support or a ventricular assist device, at the time of death, if life-prolonging therapy is withdrawn or withheld, or when the patient is transferred to a general ward or another hospital. The reason for censoring is recorded, and all data obtained until censoring will be included in the analysis.

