#### Circulatory State Transitions During Post Cardiac Arrest Syndrome

During critical illness, most patients go through different states of hemodynamic stability. We have categorized the circulatory state after CA in 3 different categories based on data obtained from routine care (Table 1). Every 10 min, a patient is classified according to the least favorable measurement at that time (eg, isolated MAP of 40 mm Hg is sufficient to classify a patient to have severely disturbed circulation).

We will validate the appropriateness of the defined categories against the cardiac index.

Patients may go back and forth between the clinical states, defined in Table 1, corresponding to the severity of their illness and its progression (Figure 2), and the changes from one clinical state to another will be recorded. By using survival analysis methodology, we allow for right censoring, which means that the information from patients with limited follow-up time can be included in the analyses. A patient who is in a certain clinical state at time *t* might remain in the same state or change to one of 2 others at time *t* +1. In such multi-endpoint settings, the clinical states compete with each other, and the transitions over time are best studied with methods developed for competing risk analyses.

**Table 1 table1:** Circulatory states.

Variables	Circulation		
	Undisturbed	Disturbed	Severely disturbed
Mean arterial pressure, mm Hg	≥65	45-64	<45
Heart rate, bpm	51-100	<50, 101-130	≤40, >130
Lactate, mmol/L	<2	2–4	>4
ScvO_2_, %	≥65	50-64	<50
Fluid resuscitation, L/hours	<0.5	0.5-1.9	≥2
Norepinephrine, μg·kg^−1^·min^−1^	<0.1	0.1-0.29	≥0.3
Dobutamine, μg·kg^−1^·min^−1^	No	<10	≥10
Vasopressin	No	No	Yes
Epinephrine	No	No	Yes
Levosimedan	No	No	Yes
Aorta balloon pump	No	No	Yes

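### Death, mechanical support, withdrawal of therapy and transfer are censored in a three-state Aalen-Johansen analysis, so its probabilities describe a cohort that nobody leaves

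*Protocol article*

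**What the plan says.** The Censoring section of the protocol article lists the events that end follow-up. It begins "Patients are censored from further follow-up if the patient undergoes acute cardiothoracic surgery or intervention with extracorporeal membranous oxygenation support" or a ventricular assist device, and continues "at the time of death, if life-prolonging therapy is withdrawn or withheld, or when the patient is transferred to a general ward" or to another hospital. It adds: "The reason for censoring is recorded, and all data obtained until censoring will be included in the analysis".

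The section on circulatory state transitions handles shortened follow-up in the same way: "By using survival analysis methodology, we allow for right censoring". It describes the state space in words. A patient in one state "might remain in the same state or change to one of 2 others at time" *t*+1, and "the clinical states compete with each other, and the transitions over time are best studied with methods developed for competing risk analyses". The estimators named are Aalen-Johansen for transition probabilities and Nelson-Aalen for transition intensities.

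The section on patterns predictive of deterioration reduces the outcome to two values: deterioration, or its absence (unchanged or improved). It plans logistic regression at several time lags, and Aalen's linear model for the intensities. Table 1 makes severely disturbed circulation the worst of the three categories.

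**The concern.** The plan appeals to competing-risk methods, but in its text only the three circulatory states compete. The events that take a patient out of all three are assigned to censoring. The same section notes that Kaplan-Meier is accurate only when its two states cover every possibility. A three-state model of patients who can also die, receive ECMO or leave the unit fails that condition in the same way.

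Two things are at stake. First, a reader will naturally take an Aalen-Johansen curve for severely disturbed circulation as the share of the enrolled cohort in that state at that time. As specified, it is not. Second, a patient already in the worst category has no worse category to enter, so death or ECMO/VAD from there cannot appear as a deterioration in the prediction analysis.

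Exits need not be rare. The Introduction states that "in-hospital mortality is unchanged at around 50% to 70" percent, and assessment of hypoxic brain injury usually starts on day three or four, inside the five-day window.

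**Working it through.** The plan has no figure of its own to reproduce: the 50 patients are set without a formal calculation, and no exit rates are given. The check has four steps.

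**1. Direction, from the estimator alone.** Aalen-Johansen is the product over event times of (I + ΔÂ), where each diagonal element of ΔÂ is minus the sum of the increments leaving that state.
- With three states and exits censored, each row of ΔÂ sums to 0. Each row of the product then sums to 1, whatever the number of exits.
- With absorbing states added, the increments between circulatory states are the same, but each diagonal element is lower by the exit increment. The circulatory 3×3 block is therefore no larger in any element. Products of non-negative matrices preserve that ordering.
- So the censored version is at least as large for every circulatory state at every time. This part needs no assumed rate.

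**2. Illustrative size (all rates assumed).** Hourly Markov chain, 120 steps (5 days × 24 h), start undisturbed/disturbed/severe = 0.2/0.4/0.4.
- Hourly moves: undisturbed to disturbed 0.03, undisturbed to severe 0.005, disturbed to severe 0.03, disturbed to undisturbed 0.05, severe to disturbed 0.04.
- Hourly exits: death/ECMO 0.01 from severe and 0.001 from disturbed; transfer 0.01 from undisturbed.

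| At 120 h | Undisturbed | Disturbed | Severe | Dead/ECMO | Transferred |
|---|---|---|---|---|---|
| Exits censored, three states | 42.4% | 29.8% | 27.8% | – | – |
| Exits absorbing, whole cohort | 17.7% | 13.4% | 11.5% | 27.3% | 30.1% |
| Exits absorbing, among those still observed | 41.5% | 31.5% | 27.0% | – | – |

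The last row divides the second by 17.7 + 13.4 + 11.5 = 42.6%; for severe, 11.5/42.6 = 27.0%.

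Varying death/ECMO from severe over 0.5–2%/h and transfer over 0–2%/h (exit from disturbed held at 0.1%/h), whole-cohort P(severe) runs from 5.1% to 20.9% against a constant 27.8%. Among those still observed it runs from 21% to 32%.

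**3. A second set of assumed rates.** A continuous-time model with different intensities, and all adverse exits together scaled to 30%, 50% or 70% by day 5, gives 27% severe at 120 h when exits are censored.
- 30% adverse exits, no ward transfer: 18% of the whole cohort, 0.266/0.177 = 1.5-fold.
- 50% adverse exits, 23% ward transfer: 7%, 0.266/0.068 = 3.9-fold.
- 70% adverse exits, 25% ward transfer: 1%, 0.266/0.011 = 24-fold.

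**4. Intensities and uncounted events.** In a simulation of 20,000 patients under the step 3 model, the severe-to-disturbed rate was estimated at 0.061 against a true 0.060, and disturbed-to-severe at 0.041 against 0.040. Exits that depend on the current state do not distort these rates, because the risk sets are state-specific. Per patient there were 2.93 deteriorations between circulatory states and 0.385 adverse exits. The share of adverse moves not counted is 0.385/(0.385 + 2.93) = 12%, and 65% of those exits came from the severe state.

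For scale, 50% to 70% in-hospital mortality is 25 to 35 of 50 patients, but the protocol does not say how many die within five days.

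**The case against.** The strongest reply is that most of the gap is a choice of denominator. In the first illustration, 27.3 + 30.1 = 57.4% have left by 120 h, and among those still observed the true figures (27.0% severe, 41.5% undisturbed) are close to the censored ones (27.8% and 42.4%). That stands: this is mainly a question of which quantity is estimated. It does not remove the problem, because the plan does not say that its probabilities exclude exits, and the censored estimate is not exactly the in-unit proportion either (21% to 32% against 28% over the grid).

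Four stronger readings are tempting, and the document does not support them.
- *All multistate results are biased.* No. Nelson-Aalen and Aalen's additive model estimate cause-specific intensities, which suit questions about transitions and their predictors and survive censoring of exits, given the state and modelled covariates.
- *The worst deteriorations are never counted.* No. Data up to censoring are kept, so entry into the severe state before death or ECMO/VAD is counted. Only the terminal move is lost.
- *Such patients are recorded as not having deteriorated.* The protocol does not say how a window ending in an exit is coded.
- *Exits reflect circulatory failure.* Some do not. Ward transfer is favourable, and withdrawal after a day-three or day-four neurological assessment may have nothing to do with the circulation. Counting every death as circulatory deterioration is therefore debatable as a main analysis.

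It is also fair that Table 1 does not cover ECMO or VAD, so ending circulatory classification there is reasonable. An absorbing state does exactly that without censoring. Finally, Figure 2 is not available in the text reviewed, so the state space is read from the prose.

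**Conclusion.** The point holds for the Aalen-Johansen probabilities. The stated censoring rule and the three-state description together yield probabilities that sum to 1 and refer to a hypothetical cohort in which nobody dies, receives mechanical support or leaves. As whole-cohort probabilities they overstate every circulatory state. The direction follows from the estimator. The size (28% against 5–21% for the severe state at 120 h in one illustration, 1.5-fold to more than 20-fold in the other) rests entirely on assumed rates.

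The intensity analyses stand, provided they are presented as cause-specific and not as risks. The prediction outcome has a narrower gap: a move from the severe state to death or ECMO/VAD cannot register as a deterioration. This is a mismatch between rules that the article itself states, not detail left to a fuller plan, and it should be settled before analysis.

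**What to change.** - Use the recorded exit reasons to add absorbing states to the Aalen-Johansen analysis, for example death or withdrawal/withholding of therapy; ECMO, VAD or acute cardiothoracic surgery; and transfer out alive. Pool them if events are few.
- Reserve censoring for the end of the five days.
- Report probabilities over all states, so that the circulatory states and the exits together sum to 1.
- Label Nelson-Aalen and Aalen additive-model results as cause-specific intensities.
- In the logistic analysis, state how windows ending in an exit are handled. Do not code those ending in death or ECMO/VAD as no deterioration. Add a sensitivity analysis that counts death and mechanical support as deterioration.
- Check that Figure 2 agrees with the revised state space.

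The cost is analysis wording only, since the reasons are already collected. The downside is sparseness: three absorbing states add up to 3 × 3 = 9 possible transitions in 50 patients, which is why pooling should be allowed.

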### Sample Size

This is an observational study, and the frequency of abnormal biomarkers, circulatory states, and endpoints are largely unknown; therefore, no formal sample size calculation has been performed [24]. On the basis of a sample size from similar studies describing pathophysiology, we aim at including 50 patients [21,25].

### Routine Post Cardiac Arrest Syndrome Treatment

#### General Consideration

The treatment of the patients is decided by the physician in charge and will not be changed due to the participation in the study. The routine treatment after OHCA at St. Olav’s University Hospital will be applied unless there are specific indications for alternative strategies. Routine care is briefly outlined below.

##### Specific Cardiac Interventions

For OHCA suspected to be caused by disease in the coronary arteries, procedures for revascularization are routinely considered and performed if decided by the cardiologist. All use of medications for cardiac diseases and for anticoagulation is decided by the cardiologist in charge of treatment.

##### Therapeutic Hypothermia

According to the current practice at St. Olav’s University Hospital, the target temperature is usually 36°C. Active temperature management is performed for 24 hours.

##### Sedation and Analgesia

Sedation is initiated with either propofol or midazolam, and analgesia with either fentanyl or remifentanil. Sedation is titrated to Motor Activity Assessment Scale (MAAS) 0-1 during active temperature management and later titrated to the lowest dose achieving adequate patient comfort [26]. A muscle relaxant, cisatracurium, is not routinely used, but initiated if shivering during cooling or rewarming, and if needed to achieve adequate ventilation.

##### Cardiovascular Support

The primary treatment goal for circulatory support is to ensure adequate circulation, as evaluated by clinical examination (eg, tachycardia, pallor, cold skin, capillary refill), a mean arterial blood pressure (MAP) ≥65 mm Hg, and a urine output of ≥0.5 mL·kg^−1^·h^−1^. Generally, circulatory optimization is achieved through fluid and vasopressor administration after the following algorithm: in the presence of hypotension and/or tachycardia, the first step is to assess signs of tissue hypoperfusion (eg, cold, clammy skin and extremities, prolonged capillary refill time, diminished urine output, increasing lactate and decreasing base excess, decreasing central/mixed venous oxygenation, and if not sedated—deteriorating mental status). If the physician suspects tissue hypoperfusion, volume status is assessed through the presence of stroke volume variation >10% (pulsus paradoxus) and/or echocardiographic assessment of the heart and the inferior caval vein. If increased preload is indicated, repeated fluid boluses of 250 mL are given until cardiac output (CO) does not respond. If a fluid load is not indicated or does not improve the perfusion, vasoactive medication is administered. The standard vasoactive medications are norepinephrine and/or dobutamine, depending on whether vasoconstrictive and/or inotropic effects are indicated. If the vasoplegia is not improved by a high dose of norepinephrine (≥0.5 μg·kg^−1^·min^−1^), vasopressin (0.4 mU·kg^−1^·min^−1^) is considered.

##### Respiratory Support

Ventilation is administered by a SERVOi ventilator (Maquet Siemens, Germany). Ventilation is either pressure controlled or pressure supported for patients who have adequate spontaneous ventilation. The ventilator settings are adjusted to a positive end-expiratory pressure (PEEP) level, which give the best arterial oxygen partial pressure (PaO_2_)/fraction of inspired oxygen (FiO_2_) ratio (usually PEEP is set at 8 cm H_2_ O at the start of ventilation), a plateau pressure to give a tidal volume of 6-8 mL/kg, a respiratory rate to give a PaCO_2_ within the normal range, and a FiO_2_ to give a O_2_ saturation above 95%. Tracheostomy is considered for patients who are difficult to wean from mechanical respiratory support, usually on days 8-10 of the ICU or CCU stay.

##### Nutrition

No nutrition is given on the day of arrival to the ICU or CCU. Enteral nutrition is given as soon as possible in increasing doses (from 500 kcal/day to 1000 kcal/day to 2000 kcal/day). If enteral nutrition is not feasible or nutrition targets cannot be reached within approximately 4 to 6 days, total parenteral nutrition is gradually introduced on the fourth day (25 kcal·kg^−1^·day^−1^). Before nutrition is started, the patients receive glucose 100 g/daily. Metabolic control of blood sugar is aimed at 5-10 mmol/L by a continuous infusion of insulin. Patients who use insulin on a regular basis will receive insulin at all times, and hypoglycemia is corrected with increased glucose or nutrition administration.

##### Infection Control

Antibiotics are not given routinely, but they are introduced if there is a clinical suspicion of an infection.

